## Abstract

Photobiomodulation therapy (PBMT) with low-power laser is used for pain relief in several clinical conditions, including temporomandibular disorders (TMD). As musculoskeletal pain often produces changes in motor behavior, it is common for patients with TMD to present limited mandibular movements. To the date, there is no consensus about the optimal dosimetric parameters of PMBT for TMD. This randomized, controlled, double-blind clinical trial aims to evaluate pain relief and mandibular mobility in patients with TMD following treatments with 2 laser wavelengths, red (660 nm) and infrared (808 nm) individually and in combination as compared to a placebo treatment. One-hundred participants presenting myalgia and arthralgia, with disk displacement or not, will be selected based on the Research Diagnostic Criteria for Temporomandibular Disorders. All participants will be instructed about the etiology, prognosis, and self-care techniques for pain control on TMD, and followed up for 2 weeks. After this period, those who still present pain score over 4 in a visual analog scale (VAS) will be included in the study. Participants will be randomly assigned to 4 treatment groups: G1 = placebo (SHAM); G2 = PBMT with red laser (660 nm, 0.034 cm^2^, 88 J/cm^2^, 100 mW, 3 J/point); G3 = PBMT with infrared laser (808 nm, 0.034 cm^2^, 88 J/cm^2^, 100 mW, 3 J/point); and G4 = PBMT with red and infrared laser alternated between sessions. The treatment consists of 8 sessions, 2 times a week. The effect of the proposed therapies will be measured by: pain reduction in VAS; pressure pain threshold on TMJ, masseter and temporal muscles; and the amplitude of mandibular movements (opening, protrusion, and right and left lateral movements). The data will be collected at the following times: initial (T1), after the 1st treatment session (T2), at the end of treatment (T3), and 30 days after the last PBMT session (T4). For statistical analysis will be used 2-way repeated measures analysis of variance test, complemented by a post hoc Tukey test (*P* < .05).

## Introduction

1

Temporomandibular disorder (TMD) is referred as the 2nd most frequent cause of orofacial pain among adults.^[1]^ It is estimated that 60% to 70% of the population has at least one sign of TMD, a condition that commonly affects the masticatory muscles, temporomandibular joint (TMJ), and associated structures.^[1]^ As TMD's frequent clinical manifestation, musculoskeletal pain is usually referred to the lateral area of the face, head, and cervical region.^[2,3]^ Pain often produces changes in motor behavior,^[4]^ so it is common that patients with TMD present limitations or restrictions on mandibular movements.^[5]^ Other recurrent symptoms are joint noises, tinnitus, and aural fullness.^[6]^ The literature also relates TMD pain with sleep disorders, fatigue, lack of concentration, mood alterations, and difficulties to perform daily activities.^[7]^

Historically, occlusal therapy with stabilization splints is referred to as the most commonly used therapeutic intervention for TMD management.^[8]^ However, there is a recurrent debate on the literature questioning the role of occlusion in the development of TMD.^[6]^ Thus, the vision on the complexity of this disorder was broadened and new therapeutic approaches have been incorporated into the field research.

Recent investigations show that the photobiomodulation therapy (PBMT) has become a useful therapeutic option in the management of musculoskeletal disorders.^[9–16]^ Its mechanism of action on TMD is still not completely known, but authors have reported the induction of analgesia, the stimulus to tissue healing and remodeling, the modulation of proinflammatory chemical mediators, the induction of muscle relaxation, and the dissolution of trigger points.^[17]^

Ferraresi et al,^[12]^ in a literature review, point out that PBMT using low power lasers may increase muscle metabolic activity and decrease fatigue during physiotherapy tests. Thus, PBMT can improve the motor activity of the stomatognathic system. Bjordal et al^[13]^ suggest that PBMT can significantly reduce pain and increase joint health in chronic disorders. Recently, Panhoca et al^[14]^ conducted an investigation with different types of light sources, irradiating the TMJ masseter and temporal muscles with red LED (630 ± 10 nm), infrared (850 ± 10 nm), and near-infrared (780 nm) lasers, bilaterally. The authors reported a reduction in pain and an improvement in mouth opening in all experimental groups, with no differences among them. However, a recent systematic review points to a great divergence regarding laser therapeutic parameters, which leads to a lack of consensus regarding the validity of the PBMT for TMD care.^[15]^

Xu et al^[11]^ conducted a systematic review with meta-analysis and affirmed that laser PBMT may effectively relieve pain and improve mandibular function in patients with TMD, although the available data is scarce and the quality of the evidence considered very low/moderate. Thus, it becomes clear that there is urgency for well-designed investigations, easy to be adapted to the clinical routine, in the quest for optimal parameters for PBMT in TMD.

The purpose of this randomized controlled trial is to analyze the influence of red or infrared wavelengths, and their combination, on pain and mandibular function of patients with TMD. This trial aims to provide a better understanding of the therapeutic responses that might be achieved by a clinical innovative yet simplified approach, contributing to the construction of effective, safe and low-cost comprehensive strategies in the conservative management of TMD.

## Methods

2

### Trial design

2.1

This will be a randomized, controlled, parallel, double-blind clinical trial.

### Objectives

2.2

Primary objective:

To evaluate the efficacy of different photobiomodulation protocols (red, infrared, and red associated with infrared laser) on pain of patients with TMD.

Secondary objectives:

To assess the immediate and longitudinal impact of proposed treatments on pain and mandibular mobility.To relate pressure pain threshold (PPT) and pain under visual analog scale during a bilateral palpation examination of the TMJ, temporal and masseter muscles, at different times of the treatment.To verify, 30 days after concluding the PBMT, the duration of the therapeutic effects produced by the proposed protocols.

### Setting of the study and recruitment

2.3

Volunteers seeking for treatment at the primary care clinic of the Interdisciplinary Orofacial Pain League (Department of Stomatology, School of Dentistry, University of São Paulo, Brazil) will be screened according to the inclusion and exclusion criteria. This investigation will be conducted under the Resolution 466/2012 (Brazil's National Health Council). Participants will sign an Informed Consent Form approved by the Research Ethics Committee of the School of Dentistry, University of São Paulo (protocol n. 2,201,761), assuring they will have their identity preserved and granting the management of any unintended effects of trial interventions without any costs.

This protocol for clinical trial is registered at Brazilian Clinical Trials Registry - REBEC (www.ensaiosclinicos.gov.br) as RBR-2bnc6y, first published April 12, 2018.

### Eligibility criteria

2.4

Inclusion criteria: aged between 18 and 50 years; both genders; diagnosis of myalgia and arthralgia, with or without disk displacement; report of TMJ-related pain greater than score 4, measured with visual analog scale (VAS), after 2 weeks of guided self-care; and literate.

Exclusion criteria: patients with muco-supported dental prostheses, orthopedic, or orthodontic appliances; whose state of health contraindicates some of the therapies; presenting teeth in precarious conditions, for example, with indication of endodontic treatment; carriers of rheumatoid arthritis; who are using any analgesic, anti-inflammatory, antidepressant, and/or anxiolytic drugs; carriers of congenital problems with involvement of TMJ and/or cervical region; with recent mandibular fractures; pregnant women; and who are already being treated for TMD in another service.

### TMD diagnosis and evaluation methods

2.5

A full anamnesis and physical examination (Research Diagnostic Criteria for Temporomandibular Disorders – RDC/TMD^[18]^) will be conducted to diagnose the type of joint and muscular impairment present. Pain levels will be recorded using a VAS and the PPT, with an algometer. The mandibular function will be assessed by the width of mouth opening, protrusion, and right and left lateral jaw movements. All clinical evaluations will be performed by a single experienced researcher ([name]), blinded to group allocation.

RDC/TMD: Participants will be examined seated in a dental chair, in a room with adequate lighting, according to RDC/TMD recommendations. This examination is considered the gold-standard for research in TMD and accesses essential outcomes such as the presence of muscle/joint pain, and measures of maximum mouth opening, protrusion, right and left lateral movement, which will be measured with a digital caliper.VAS: Each participant will be instructed to draw a mark on a 10-cm straight line with the endpoints defined as “no pain at all” and “worst pain imaginable”. The distance between “no pain at all” and the mark will define the subject's self-report of pain. Patients will be inquired for overall spontaneous pain, and the intensity of pain during palpation of the TMJ, anterior temporal, and masseter muscles bilaterally (according to the RDC/TMD instructions).PPT: To a more accurate record of the pain experience, a digital algometer (Pain Test FPX 25 Algometer; Wagner Instruments, Greenwich, USA) will be used to apply a controlled pressure at a 90° angle on the areas to be investigated (TMJ, anterior temporal, and masseter muscles bilaterally). This equipment has a circular probe of 1 cm^2^; the movement will be executed at a uniform and constant speed (0.5 kgf/cm^2^/s).^[19]^ Participants will be instructed to say “stop” at the point that the test becomes painful. The same anatomic area will be tested three consecutive times, and the average of the value displayed (kgf) will be recorded as the PPT.

### Experimental groups

2.6

All participants will undergo guided self-care educational measures for pain control in TMD. They will be instructed about the etiology and prognosis of TMD, the importance of the suspension of parafunctional habits and physical therapy strategies to pain control in TMD (such as exercises and heat therapy),^[20–22]^ during one-a-one sessions by an experienced physician ([name]). All subjects will be warned to not take any analgesic or anti-inflammatory medication during the study and to inform the professional if they started any medical treatment. Those who succeed in following the instructions for 15 days and still return with pain over score 4 in VAS will be invited to join this study. The participants will be randomly allocated into 4 groups as described in Table 1.

**Table 1 T1:**
[figure not shown]
Experimental groups and correspondent treatment.

Once a participant is enrolled, the attendants ([name], [name]) will make effort to assure patients retention for the entire study period with systematic methods for scheduling appointments and direct e-mail/phone contact as reminders for the consults.

### Interventions

2.7

The 1st clinical session corresponds to a lecture on the etiology and prognosis of TMD, as well as recommendations for parafunctional habits avoidance and self-management of pain without medications.^[23–25]^ All participants will be followed-up for 2 weeks to check compliance with the educational measures and no-medication intake. Only the participants who still present pain in a VAS over score 4 after 2 weeks of self-management will be invited to join the study.

### Protocols for PBMT

2.8

All participants will undergo PBMT according to the group to which they were allocated. The assigned group will be only revealed to the researcher responsible for the irradiation ([name]) by the time of the first PBMT session, after the 2-week educational measurements and initial evaluations (T1). The PBMT will be performed twice a week, totaling 8 sessions (4 weeks).

The G1 group (SHAM) will undergo a PBMT simulation. Negative control treatment will be held with a SHAM-equipment (DMC, São Carlos, Brazil) of the same design as the active equipment, simulating a PBMT session since it's able to emit an inert guide light (with no power), and reproduce the time marker's sounds identically to the active one.

The G2 group will be irradiated with an InGaAlP red laser (Therapy XT; DMC), 660 nm, 88 J/cm^2^, 100 mW, 30 s/point, spot size 0.034 cm^2^, 3 J/point, in continuous mode and with the tip positioned at 90° in contact with the skin.

The G3 group will be irradiated with an AsGaAl infrared laser (Therapy XT; DMC), 808 nm, 88 J/cm^2^, 100 mW, 30 s/point, spot size 0.034 cm^2^, 3 J/point, in continuous mode and with the tip positioned at 90° in contact with the skin.

The G4 group will be irradiated in the odd sessions with red laser (InGaAlP, 660 nm), following the G2 protocol; and in the even sessions, with infrared (AsGaAl, 808 nm) as described for the G3 protocol.

The equipment was previously calibrated and the output power is periodically checked using a power meter (Laser Check; MMOptics LTDA, São Paulo, Brazil). A summary of the irradiation parameters is shown in Table 2.

**Table 2 T2:**
[figure not shown]
Photobiomodulation therapy protocols.

To investigate the effect of the PBMT on painful experience around the TMJ, the laser light will be applied in 2 points: anterior to the mandibular condyle and intra-auricular toward the TMJ. The masticatory muscles will also be accessed, with a 2-point irradiation on the superficial masseter muscle and 2 points on the anterior temporal muscle bundle. The irradiation points will be equally distributed within the muscle area. The laser application points will be the same for all groups, bilaterally, and is exemplified in Figure 1. Safety measures for infection control, waste disposal, and protection from radiation by the operator and patient will be implemented in all therapy sessions.

**Figure 1 F1:**
[figure not shown]
Irradiation points: anterior to the mandibular condyle (A) and intra-auricular toward the temporomandibular joint (B), 2 points on the superficial masseter muscle (C, D), and 2 points on the anterior temporal muscle bundle (E, F). Source: Adapted from mikomo/iStock.com.

### Outcomes and data collection

2.9

Evaluations will be performed by a single trained examiner ([name]) who is blinded to the allocation of the participants within the different treatment groups. Measurements will be performed at the following times: initial (T1), immediately after the 1st PBMT session (T2), at the end of the treatment (T3), and 30 days after the end of therapies (T4).

The primary outcome of the study will be pain reduction (baseline – 4 weeks) according to a visual analog scale of 10 cm. Pain reduction will be expressed in centimeter, as mean group values.

Secondary outcomes will be:

1.Pressure pain threshold in the TMJ, masseter, and anterior temporal muscles, bilaterally, with a digital algometer, registered in kgf (Pain Test Algometer FPX 25; Wagner Instruments).2.Extension of mandibular range of movement, such as mouth opening (taking into consideration the overjet), protrusion (added the overbite), and right and left mandibular movement (noting possible midline deviation) in centimeter, with the aid of a digital caliper.

At each PBMT session, spontaneously reported adverse events and other unintended effects of trial interventions will be registered and managed according to the participant's need.

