### Statistical analysis

2.15

Statistical analysis will be conducted to compare the 4 groups of treatment, concerning the change from baseline of primary and secondary outcomes. Regarding the primary outcome, the groups will be compared using test of comparison of means. If there is adherence to a normal distribution and homogeneity of variances, the groups will be compared by analysis of variance (ANOVA; 2-way repeated measures ANOVA with post hoc Tukey Test). The analysis will be performed by intention to treat, with the imputation of data by carrying forward the last observed outcome in the case of missing data.^[26]^ Groups will be compared as regards other outcome using repeated measures ANOVA or a Chi-squared test. All tests will be conducted considering a 5% alpha.

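### Section 2.9 pairs the incisal corrections with the wrong movements (overjet with opening, overbite with protrusion), which affects absolute ranges but not changes from baseline

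*Protocol article*

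**What the plan says.** Outcomes and data collection (2.9) lists mandibular range of movement as the second of two secondary outcomes. It gives opening and protrusion as "mouth opening (taking into consideration the overjet), protrusion (added the overbite". Lateral movement is described as "right and left mandibular movement (noting possible midline deviation) in centimeter, with the aid of a digital caliper"; that correction is not in question.

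TMD diagnosis and evaluation methods (2.5) lists the same movements under the RDC/TMD examination, as "measures of maximum mouth opening, protrusion, right and left lateral movement, which will be measured with a digital caliper". It mentions no incisal correction, so it neither repeats the wording of 2.9 nor corrects it. Section 2.9 is the only place in the article that says how the overlaps enter the measurement.

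Statistical analysis (2.15) says that the four groups are compared "concerning the change from baseline of primary and secondary outcomes", and names repeated-measures ANOVA among the methods.

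**The concern.** The two terms refer to different axes. Overbite is the vertical overlap of the upper and lower incisors, and overjet is the horizontal distance between them. A caliper reading of opening between the incisal edges leaves out the vertical distance the lower incisors travel before the edges meet, so the overbite completes it. A reading of protrusion taken as the forward reach past the upper incisors leaves out the horizontal distance needed to draw level, so the overjet completes it. Section 2.9 has these the other way round. The reciprocal pattern looks like a transposition and not a deliberate choice.

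If the examiner follows the text, the absolute opening and protrusion reported for each group and visit would be wrong for every participant whose overbite and overjet differ. The same offset matters proportionately more for protrusion, which is the smaller movement. Anyone repeating the method from the article would copy the error.

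**Working it through.** The article states no figure for this point, so there is nothing to reproduce. The check is algebra on the definitions in 2.9.

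**Inputs**
- OB = overbite (vertical) and OJ = overjet (horizontal). The article gives no values. Assumption: each lies between 0 and 5 mm.
- I = interincisal distance at maximum opening; F = forward reach past the upper incisors.
- From 2.9: OB is added to protrusion. OJ is considered for opening with no operation stated. Assumption: it is added.
- From 2.15: groups are compared on change from baseline.

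**Error in absolute values**
- Opening: intended I + OB; as written I + OJ; error = OJ - OB.
- Protrusion: intended F + OJ; as written F + OB; error = OB - OJ.

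The errors are equal in size, opposite in sign, and zero only if OJ = OB. Over the assumed range the extremes are 0 - 5 = -5 mm and 5 - 0 = +5 mm (-0.5 to +0.5 cm in the units of 2.9).

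**Illustration with assumed values, OB = 4 mm and OJ = 2 mm**
- Opening error: 2 - 4 = -2 mm (recorded too small).
- Protrusion error: 4 - 2 = +2 mm (recorded too large).

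**Error in change from baseline, same participant**

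| Measure | Raw reading, T1 to T3 (assumed) | Change, intended correction | Change, as written |
|---|---|---|---|
| Opening | 35 to 40 mm | (40 + 4) - (35 + 4) = 5 mm | (40 + 2) - (35 + 2) = 5 mm |
| Protrusion | 5 to 7 mm | (7 + 2) - (5 + 2) = 2 mm | (7 + 4) - (5 + 4) = 2 mm |

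The change is the same under either correction, because the same OB and OJ enter at each visit.

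**Repeated-measures ANOVA on raw scores**

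Write the recorded value as the intended value plus a participant constant d, the same at T1 to T4. The time and group-by-time terms depend only on differences between visits within a participant, so d drops out. The group main effect depends on each participant's mean over visits, which becomes the intended mean plus d. That term therefore carries any chance difference between groups in mean d. If d is unrelated to the true range, it also carries the extra between-participant variance of d. Carrying the last observation forward (2.15) does not alter this, because the carried value contains the same d.

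**The case against.** The strongest reply is that this is one parenthesis in a condensed article. Section 2.5 ties the measurement to the RDC/TMD examination and to a single experienced examiner. A drafting slip is at least as plausible as a systematic measuring error. That stands: the article shows a wrong definition, not wrong data. A reader might infer that the measurements of the participants already included are wrong, but nothing in the article says which overlap was actually applied.

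The second reply is that no planned treatment comparison changes. This also stands for the scale named in 2.15. A reader might infer that the swap biases the mobility results, or adds noise throughout the repeated-measures ANOVA. It does neither: the offset is absent from change scores and from the time and group-by-time terms, and can reach only the group main effect on raw scores. Nor does the article plan to read opening or protrusion against a normal range, and Eligibility criteria (2.4) sets no threshold on either.

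The third reply is that the size for opening depends on an operation that 2.9 leaves open. This is correct. The formula for opening is conditional on addition; for protrusion, addition is stated.

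None of this rescues the wording. It sits in the outcome definition, pairs each term with the wrong axis, and is not corrected elsewhere in the article.

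**Conclusion.** The definition in 2.9 is wrong as written, and the point is minor. Followed literally, absolute protrusion is off by OB - OJ, and absolute opening by OJ - OB if the overjet is added. If each overlap is assumed to lie between 0 and 5 mm, that is -5 to +5 mm per participant, and nil where the two are equal. The harm is confined to reported absolute means at T1 to T4 and to any between-group main effect on raw scores.

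The conclusion rests on the ordinary meaning of overbite and overjet, which the article does not define, and on both being constant within a participant over the study. The primary outcome (VAS pain) and the sample size do not depend on these measures. The article does not support a claim that recorded data are wrong or that the planned change-from-baseline comparison is biased.

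**What to change.** In 2.9, exchange the two terms so that opening is corrected for overbite and protrusion for overjet. State the operation for opening as explicitly as it is already stated for protrusion.

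Confirm with the examiner which correction was applied to the 40 participants reported as included under Trial status (3.1). Where the wrong one was used and both overlaps were recorded, recompute:
- protrusion = recorded value - OB + OJ;
- opening = recorded value - OJ + OB, if the overjet had been added.

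The article does not say whether both overlaps were recorded. Where they were not, flag those absolute values when they are reported; the changes from baseline remain usable.

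The cost is a short text correction and a check of existing records, with no new visits. With 100 participants planned, 100 - 40 = 60 were still to be included, so the corrected wording would govern most of the measurements.

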Another much-discussed topic is the mode and frequency of application for PBMT on TMD. The review by Herpich et al^[15]^ points out that the treatment protocols reported in the selected publications ranged from 1 to 20 laser sessions, with frequencies varying from 1 to 5 times a week. Furthermore, as for the irradiated area, some studies recommend laser application at predetermined points,^[19,36]^ others at acupuncture points,^[37]^ while some recommend the irradiation of trigger points.^[38,39]^ The evidence for the best laser application site and frequency for managing TMD's symptoms is insufficient, making it difficult to compare previously published protocols.

The effectiveness of PMBT for TMD has been considerably discussed^[11,15,35]^ mostly due the great divergence of the parameters used or insufficient data report constraining the clinician to replicate the PBMT protocol. Also, few clinical studies tested the performance of PBMT combining red and infrared laser irradiation for patients with TMD. This investigation will contribute to enlighten a evidence-based practice of PBMT for TMD, by reporting the effects of specific wavelengths on pain and mandibular function of individuals with myalgia and arthralgia.

A limitation of the study is that the care provider cannot be blinded to allocation, due to the nature of the intervention. Henceforward, this professional is instructed not to reveal the allocation status of the participant at the follow-up assessments, until separated datasheets for further analysis are complete.

Randomized clinical trials are the best source of scientific evidence to determine the efficacy of an intervention and serve as a reference for decision-making by health professionals. Clinical trials should be analytical, prospective, with the hypotheses to be tested described a priori, randomized, blinded and experimental to fulfill this referential function; therefore, the quality of these studies is of paramount importance.

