### Trial status

3.1

Participants recruitment began at February 2018 and it is expected to end at October 2021. As shown on Figure 3, 1545 volunteers were screened, 457 participants fitted the study's inclusion criteria, 325 participants were discharged according to exclusion criteria, 132 received the educational measures, and only 40 were included in the study (34 women and 6 men, aged 19–43 years old, mean age 28.4 years). No side effects have been reported so far.

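### Adverse-event registration is tied to spontaneous reports at treatment sessions, so the 30 days to T4 have no stated registration (minor)

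*Protocol article*

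**What the plan says.** The only collection rule for harms is the last sentence of section 2.9: "At each PBMT session, spontaneously reported adverse events and other unintended effects of trial interventions will be registered". It fixes both the method (spontaneous report) and the occasion (the PBMT session).

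The surrounding design is as follows:

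- **Length of treatment (section 2.8).** "The PBMT will be performed twice a week, totaling 8 sessions (4 weeks".
- **Visits around and after the last session (section 2.9).** Measurements are made "at the end of the treatment (T3), and 30 days after the end of therapies (T4". One examiner, blinded to allocation, makes them.
- **Who knows the arm.** Under sections 2.8 and 2.12 the researcher delivering the laser opens the envelope and learns the group. The Discussion (section 3) lists as a limitation that "the care provider cannot be blinded to allocation, due to the nature of the intervention".
- **Objectives and outcomes (sections 2.2 and 2.9).** These cover pain, pressure pain threshold, mandibular movement and duration of effect at 30 days. Safety is in neither list.
- **Safety wording.** The purpose statement in the Introduction speaks of "contributing to the construction of effective, safe and low-cost comprehensive strategies". Section 3.1 says of the 40 participants included at that point: "No side effects have been reported so far".

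**The concern.** An article can leave adverse-event procedures to the full protocol. Here, however, the article states a rule, and the rule is narrow. Taken as written, it stops at the last laser session, while the trial goes on to measure benefit for another 30 days. Lasting benefit at T4 is an objective, but symptoms that arise over the same period have no stated place to be recorded.

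The second issue is the setting. Registration is attached to the sessions, and the person running them knows the arm. If that person also writes down the events, knowledge of the arm can affect what is prompted, judged relevant and recorded. The blinded examiner, who could avoid this, is given the efficacy measures but not adverse events.

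At stake is how a later report of few or no events is read. It may be taken to cover the whole follow-up and to compare the active arms fairly with sham, and the stated rule secures neither. Efficacy conclusions are not at risk.

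**Working it through.** **1. Period without stated registration.**
Inputs: 8 sessions, twice weekly, over 4 weeks (section 2.8); T4 at 30 days after the end of treatment (section 2.9).
The article does not give the day of session 8. Eight sessions have seven gaps of about 3.5 days, so 7 × 3.5 = 24.5, or about day 25. Counting the full four weeks gives day 28.

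- Session 8 at day 25: 30 / (25 + 30) = 30/55 = 54.5%.
- Session 8 at day 28: 30 / (28 + 30) = 30/58 = 51.7%.

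So 52% to 55% of the time from first session to T4 lies outside the stated rule. This is calendar time, not a share of risk; nothing in the article says how events would be spread over it.

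**2. Who sees the participant, and when.**

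| Occasion | Person named | Knows the arm? | Adverse-event registration stated? |
|---|---|---|---|
| PBMT sessions 1 to 8 | Laser operator | Yes | Yes, spontaneous reports; recorder not named |
| T3, end of treatment | Examiner | No | Not in its own right |
| T4, 30 days later | Examiner | No | No |

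The article does not say whether T3 falls on the day of session 8. If it does, reports made that day are covered by the session rule. T4 is not covered on any reading of the visible text.

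**3. What zero events could show, even with complete collection.**
The exact one-sided 95% upper limit with no events in n participants is 1 − 0.05^(1/n).

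- One arm, n = 25: 1 − 0.05^(1/25) = 11.3% (12.2% with the 23 per arm of section 2.10).
- Three active arms pooled, n = 75: 1 − 0.05^(1/75) = 3.9% (4.2% with 3 × 23 = 69).
- The 40 included so far, all arms: 1 − 0.05^(1/40) = 7.2%. Section 3.1 does not say how many of them had finished treatment or reached T4.

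These limits assume that every event is captured. Under the stated rule they could describe the treatment weeks at most. The arm size restricts precision whatever the collection method.

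**4. Sample size.**
The planned 23 per group rests on the VAS outcome. It is reproduced by a four-group ANOVA with a 2.5 cm largest difference, the other two means midway, SD 2.5 cm and alpha 5% (power 80.4%). Nothing in it depends on how adverse events are collected.

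**The case against.** The case against making much of this is substantial, and most of it stands.

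- **A reader might infer that the trial fails a safety claim it set out to make.** The article does not support this. The word *safe* occurs in a general statement of purpose, and safety is neither an objective nor an outcome. The note in section 3.1 reports status and draws no inference.
- **A reader might infer that the unblinded operator is the recorder.** This is plausible, because registration is attached to the sessions, but it is not written. The sentence is passive and sits in a section that opens with the blinded examiner, who also measures immediately after session 1. Participants are blinded by a matching sham device, so volunteering itself should not differ through knowledge of the arm. Any bias would come in eliciting, judging and recording.
- **A reader might infer that late events are never captured.** That goes too far. The schedule in Figure 2 is not shown, section 2.3 promises management of unintended effects without a time limit, and section 2.6 asks participants to report any medical treatment they start. None of these is a registration rule for T4, but they rule out a flat *never*.
- **A reader might infer that nothing counts unless volunteered.** The qualifier may apply to adverse events alone and not to the other unintended effects in the same sentence.
- **Spontaneous against solicited reporting is partly a design preference,** and the rule is the same in all four arms. A change after 40 inclusions mixes two methods.

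The T4 gap remains. Preferring spontaneous reports does not explain it, because even a spontaneous report at T4 falls outside the stated rule.

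**Conclusion.** The point holds as a minor one. In the visible text, adverse-event registration ends with the treatment sessions, leaving 30 of about 55 to 58 days (52% to 55%) from first session to T4 without a stated rule, although a blinded visit for every participant closes that period. As written, the trial could describe events spontaneously reported during about four weeks of treatment. It could not support a statement about harms through T4. A comparison of event counts between arms would be open to recorder bias if the operator does the recording.

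This rests on three assumptions: that Figure 2 does not schedule adverse-event registration at T4, that session 8 falls between about day 25 and day 28, and, for the bias part only, that the operator is the recorder. The amount of under-recording cannot be estimated from the article. The primary analysis, the sample size and all listed objectives are unaffected.

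**What to change.** Extend adverse-event registration to T3 and T4. At both visits the blinded examiner asks one open question, worded identically in all four arms, on whether the participant has noticed any new or worse symptom since a stated earlier point. Name who records events at the treatment sessions. Report counts by arm with exact 95% confidence intervals, and identify participants enrolled before the change.

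If Figure 2 or the full protocol already schedules this at T4, bring section 2.9 into line with it. If the change is not made, limit any safety wording to events spontaneously reported during the treatment sessions.

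The cost is one line on existing visit forms and about a minute per visit, with no new visit or staff. At the reported status 100 − 40 = 60 participants were still to be included, so most could be covered. The downsides are more non-specific complaints in every arm, sham included, and two ascertainment methods across the recruitment period, which must be disclosed. The change concerns data collection only, not treatment.
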